## Abstract

**Background:**

Aged polymedicated patients are particularly vulnerable for drug-related problems. A medication review aims to optimize the medication use of patients and improve health outcomes. In this study, the effect of a pharmacist-led medication use review is investigated for polymedicated ambulatory older patients with the aim of implementing this pharmaceutical care intervention across Belgium.

**Methods:**

This article describes the study protocol of the SIMENON study and reports the results of the feasibility study, which aimed to test and optimize this study protocol. In the SIMENON intervention study, 75 Belgian community pharmacies each recruit 12 patients for a medication use review. For each patient, the identified drug-related problems and subsequent interventions are registered using the PharmDISC classification. In a subset of Dutch speaking patients, a pretest-posttest single group design is used to measure the impact of this review on patient related outcomes using questionnaires. The main outcome of the study is the type and number of drug-related problems and related interventions. A second outcome is the impact of the medication use review on adherence, objectively measured with dispensing data. Evolution in medication related quality of life is another outcome, measured with the Living with Medicines Questionnaire version 3. Other patient reported outcomes include adherence, self-management, patient satisfaction, fall incidents and use of emergency healthcare services.

**Discussion:**

The findings of this study can provide data on the effectiveness of a medication use review in the Belgian primary care setting. Furthermore, it will provide insights in which patients benefit most of this intervention and therefore facilitate the implementation of medication review in Belgium.

**Trial registration:**

ClinicalTrials.gov NCT03179722. Retrospectively registered 7 June 2017.

## Background

Aging populations, increase in chronic conditions and polypharmacy are challenging healthcare systems worldwide. In Belgium 17.9% of the population is aged 65 or more and at least 19% of these patients are polymedicated [1]. Polymedication entails a risk for drug-related problems such as non-adherence, drug interactions, adverse drug events and hospitalizations [2]. Approximately 6 to 17% of acute hospitalizations in older patients are drug-related [3, 4]. In Belgium 42.000 medication-related hospital admissions are potentially preventable per year and could save 200 million euros on a yearly basis [3–5].

A medication review is defined as “a structured evaluation of a patient‘s medicines with the aim of optimizing medicines use and improving health outcomes. This entails detecting drug-related problems and recommending interventions” [6]. Depending on the sources of information used in the review, three types are distinguished: a basic, intermediate and advanced medication review [6]. Evidence exists that medication reviews can improve outcomes such as adherence, appropriateness of prescribing and emergency department contacts [7–9]. However the evidence for an impact on the number of hospitalizations is contradicting [7, 10].

The rising trend of medication review services in healthcare is undeniable [11]. In countries such as Australia, The Netherlands, The United Kingdom, Portugal, Denmark and Switzerland medication reviews are a nationally implemented reimbursed healthcare service [11]. Contrasting, the target population for an intermediate medication review differs across countries and further research should identify and target patients who would benefit most of a review [8, 11].

The implementation of clinical services by pharmacists in Belgium is also progressing. Since 2013, Belgian pharmacists offer an advanced pharmaceutical care service for new asthma patients. Moreover the federal government has funded research on advanced medication reviews in Belgian nursing homes [12]. Similarly, the Association of Belgian Pharmacies has now taken initiatives to investigate and implement intermediate medication reviews in primary care. For that purpose, a consortium with three Belgian universities was set up to prepare and research the implementation of this type of review, further referred to as medication use review (MUR), in Belgian community pharmacies.

In a first step, a feasibility study was conducted to test the medication review six step process. The protocol, study materials and measures were optimised based on the feedback of these participants. In a second step, the objective is to Study the Impact of a Medication use EvaluatioN by the cOmmuNity pharmacist (SIMENON study) in older polymedicated patients. Other members of the consortium will focus on the added value of the standard application of the GheOP^3^S tool^1^ (to evaluate appropriateness of prescribing) and multidisciplinary case conferences during the medication review process [13]. Furthermore, thorough research on the implementation of the service will be performed using the RE-AIM model [14].

## Methods/design

This study protocol is developed in line with SPIRIT recommendations for reporting clinical trial protocols [15].

### Design, setting and study period

The SIMENON study is an intervention study with a pretest-posttest single group design. The intervention is performed by community pharmacists in the primary care setting. Patients are followed over a period of 9 months. Patient recruitment was planned from November 2016 until March 2017.

### Pharmacy

Pharmacies in the three regions of Belgium (Flanders, Brussels and Wallonia) could participate. Recruitment of Belgian pharmacies occurred in the fall of 2016 via national and local pharmaceutical magazines. No inclusion criteria were set but participation to the study workshop (see 6. Education program) and a signed collaboration agreement are required. Multiple pharmacists within one pharmacy can perform medication reviews. Participation comprises of performing twelve medicines use reviews, registering the findings in a webtool and delivering medication refill records of the participating patients to the research team.

### Patient

Four patient inclusion criteria are set: patients should be 70 years or older, use five or more drugs chronically (both prescription or non-prescription drugs) and live in the ambulatory setting. The age limit is set at 70 years. Given the high population of patients aged 65 or older in Belgium (approximately 2 million people), the researchers wanted to further limit the size of the eligible study population. In line with the aging population, several projects have been conducted in primary care in Belgium which focused on patients aged 70 or more instead of 65 [16]. Finally, the patient should obtain his medication from this pharmacy on a regular basis. Patients can be Dutch or French speaking. Dutch patients are also invited by their pharmacist to participate to questionnaires for a pretest-posttest measurement. Having a medication overview or the presence of a carer or home nurse are no exclusion criteria since the patient remains involved in his medication use and/or medication experiences. Carers are allowed to accompany the patient for the medication review.

### Recruitment and consent

Based on the suggestions in the feasibility study (see 12. Feasibility study), pharmacists are required to approach each patient who meets the inclusion criteria on fixed inclusion days to avoid selection bias. Upon informed consent, Dutch speaking patients are proposed to fill out questionnaires (see 9. Data collection). Patients can indicate if they prefer to be contacted by the research team either by phone, by e-mail or by letter to complete the surveys.

### Intervention

The intervention consists of a medication use review. In this intermediate medication review both a patient interview and medication refill records are used as information sources to identify drug-related problems with a specific focus on the medicines use of the patient [6]. Table 1 shows the six components of the intervention which is based on the Systematic Tool to Reduce Inappropriate Prescribing (STRIP) tool [17]. A checklist is available for participants to ensure the quality of the medication reviews (available upon request). The feasibility study confirmed the applicability of this six step process and estimated a workload of 120 min per review.

**Table 1 Tab1:** The six-step process of a medication review [17]. The time points of data collection for the SIMENON study are indicated. Both the community pharmacists (CP) and the researchers (R) collect data at different time points

	Component	Time point	Data collection	
Medication review	1 Patient recruitment	T_-1week_	R	
	2 Preparation			CP
	3 Patient interview	T_0_		CP
	4 Pharmacotherapeutic analysis			
	5 Discussing medication list	T_2weeks_		CP
		T_3weeks_	R	
	6 Follow up	T_6weeks_		CP
		T_12weeks_	R	

Upon patient recruitment, the patient is invited for a pharmacotherapeutic anamnesis also referred to as a patient interview [17]. This interview can be either on appointment, during the next visit or immediately upon consent. Patients are encouraged to bring their medication (brown bag method) to this interview and list their current medication. The anamnesis should preferably take place in the pharmacy, if possible in a private area. In exceptional circumstances such as patient immobility, the pharmacist can perform the anamnesis at the patients’ home. In preparation for the anamnesis, the pharmacist consults the medication refill records to review adherence and check drug interactions.

The aim of the patient interview itself is to gain insight in the pharmacotherapy of the patient. Data on medication use, medication knowledge but also experiences are gathered. Additional questions relate to non-medication treatments, lifestyle, living situation, allergies, functional status, hospitalization and fall incidents.

Subsequently, the pharmacist performs a pharmacotherapeutic analysis to identify drug-related problems with particular focus on the medication use. Next, priorities are set and interventions are prepared. The minimal output of a medication review is a medication overview for the patient. This overview comprises the current chronic medication of the patient, both prescribed and non-prescribed. Aside from the name of the medication, also the frequency and time of intake and remarks are registered in this overview.

In the fifth step, the pharmacist and patient reconvene to discuss and execute the interventions. The pharmacist runs through the medication overview with the patient and checks if everything is understandable for the patient. It is recommended to perform this second consultation within 2 weeks after the anamnesis. Finally, in the follow up conversation the pharmacist investigates if the undertaken actions were useful and investigates if new problems have emerged or new interventions are required. If necessary, the medication overview is updated. It is recommended to perform this follow up a month after the second patient-pharmacist conversation.

Although the medication use review is initiated by the community pharmacist, collaboration with the general practitioner (GP) is encouraged. For instance by informing the GP before the anamnesis, by actively discussing the pharmacotherapy of the patient during the analysis or by sharing the medication overview of the patient. The feasibility study uncovered there was no consensus on how the general practitioner should be involved in the review process. There was no support to organize interdisciplinary case conferences for each patient, nor to inform the GP before each review. Depending on the drug-related problems that are discovered, discussion with the GP or patient referral may be necessary.

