### Data collection

An overview of the data collection strategies is shown in Table 3. Four types of quantitative data are collected: drug-related problems and interventions, medication refill records, patient questionnaires and descriptive pharmacist information. If patients would withdraw consent, no additional data is registered but existing data is preserved.

**Table 3 Tab3:** Overview of the data collected for the SIMENON study

Data collection	A. Drug-related problems & interventions	B. Adherence	C. Questionnaires	D. Descriptive pharmacist information
Subject	Patient	Patient	Patient	Pharmacist
Collector	Pharmacist	Pharmacist	Researcher	Pharmacist
Sample size	900 patients	900 patients	140 patients	75 pharmacies
Method	Questionnaire: webtool	Medication refill records	Questionnaire: by letter, by phone or by e-mail	Questionnaire
Frequency	Four times	Once	Three times	Once
Timeframe	During the medication review process	• 9 months before • 9 months after the review	• 1 week before the review • 3 weeks after the review • 12 weeks after the review	Before start of the study
Content	• Administrative and medical data • DRPs and interventions • Duration • GP contacts	Medication refill records	• Adherence • Self-management • Polypharmacy burden • Satisfaction • Demographic data • Use of emergency healthcare services • Fall incidents	• Pharmacy and Pharmacist characteristics • Pharmacist experiences

For each patient receiving a review, an online registration form is completed by the pharmacist via a webtool (available upon request). Pharmacists are required to login to use this webtool and only coded patient information can be registered. Drug-related problems and interventions are registered throughout the medication review process using the PharmDISC classification system [18]. Permission was given by the authors to translate and use the instrument. Participating pharmacists are given a manual with explanation and examples to ensure the quality of the classification. Medication refill data is collected of all participants in the study to estimate adherence before and after the medication review. Data is collected from 9 months before until 9 months after the review. Finally, all participating pharmacists are required to fill in a questionnaire related to pharmacy and pharmacist characteristics.

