The effectiveness of a medication use review is evaluated using patient reported outcomes. Patients are surveyed at three time points by the research team of KU Leuven (Table 4). Based on the preferences of the patient the questionnaires can be completed by e-mail, by phone or by mail. These surveys allow an insight in patient experiences. Table 4 provides an overview of instruments and the time points of data collection. Permission was given by all authors to use the instruments. The ‘Living with Medicines Questionnaire’ and the ‘Patient Satisfaction with Pharmacist Services Questionnaire’ were translated by the researchers in accordance with ISPOR guidelines [20].

**Table 4 Tab4:** Patient related outcome measures. Data is collected 1 week before the patient interview (T_-1w_), 3 weeks later (T_3_) and 12 weeks after the patient interview (T_12w_)

Subject	Instrument	Authors	T_-1w_	T_3w_	T_12w_
Adherence	Probabilistic Medication Adherence Scale (ProMAS)	Kleppe et al. 2015 [21]	X		X
Self-management	Patient Activation Measure (PAM)	Hibbard et al. 2004 [22]	X		X
Polypharmacy burden	Living with Medicines Questionnaire (LMQ)	Krska et al. 2014 [23]	X	X	X
Satisfaction	Patient Satisfaction with Pharmacist Services Questionnaire (PSPSQ) 2.0	Sakharkar et al. 2015 [24]		X	
Demographic data	Living with Medicines Questionnaire (LMQ)	Krska et al. 2014 [23]	X	X	X
Use of emergency healthcare services	/		X		X
Fall incidents	/		X		X

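### The interview may take place on the day of consent, but the pretest is due a week before it; for questionnaire patients interviewed that day, the baseline would ordinarily come after the intervention has started

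*Protocol article*

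**What the plan says.** The Protocol article makes four statements that bear on the order of pretest and interview.

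- **Intervention:** three timings are allowed for the interview. "This interview can be either on appointment, during the next visit or immediately upon consent". The interview is component 3 of the review and is labelled T0 in Table 1 ("Table 1 shows the six components of the intervention"). Table 1 places recruitment, with data collection by the researchers, at T-1week.
- **Data collection, Table 3:** the first questionnaire is due "1 week before the review".
- **Data collection, Table 4:** the caption repeats this with the interview as anchor: "Data is collected 1 week before the patient interview". LMQ, ProMAS, PAM, emergency care use and falls all have a T-1w measurement. Satisfaction is measured at 3 weeks only.
- **Recruitment and consent:** "Upon informed consent, Dutch speaking patients are proposed to fill out questionnaires". Collection is remote: "Patients can indicate if they prefer to be contacted by the research team either by phone, by e-mail or by letter to complete the surveys". Data collection confirms who does it: "Patients are surveyed at three time points by the research team of KU Leuven".

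Nothing in the article keeps questionnaire patients out of the same-day option, makes the interview wait for the pretest, or exempts these patients from the one-week timing.

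**The concern.** Two stated procedures cannot both be followed for the same patient. If consent and interview fall on one day, no week exists in which to collect the pretest. A questionnaire sent by letter will arrive after the interview, and contact by phone or e-mail would ordinarily follow it as well.

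For these outcomes the study follows one group with no control, so the pretest is the only comparator. The LMQ is named under Sample size as the main outcome of the questionnaire subset. The interview gathers information on medication use, knowledge and experiences, which overlaps with what the questionnaires ask. It also asks about falls and hospitalization. Answers given afterwards may already reflect the interview. An analysis plan can exclude such a baseline, but it cannot recover one that was never taken before T0.

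**Working it through.** **1. The subset concerned.** The inputs come from Sample size and Table 5: 35 Flemish pharmacies, 12 patients each, 2/3 agreeing to questionnaires, 50% drop-out.

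- 35 × 12 = 420 patients
- 420 × 2/3 = 280 start the questionnaires
- 280 × (1 − 0.50) = 140, which reproduces the plan's figure

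The other 900 − 280 = 620 planned patients have no pretest, so a same-day interview conflicts with nothing for them.

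**2. The timings side by side.**

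| Interview option | Gap from consent to T0 | Gap the pretest needs | Compatible? |
|---|---|---|---|
| By appointment | can be set to 7 days or more | 7 days | yes, if so arranged |
| At the next visit | not stated | 7 days | not guaranteed |
| On the day of consent | 0 days | 7 days | no |

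Questionnaires are offered only after consent, so the pretest cannot be moved earlier to rescue the last row.

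**3. Effect on the estimated change.** Let Δ be the true mean change, f the share of analysed questionnaire patients whose pretest came after T0, and g the share of Δ already present in those late pretests.

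- Patients with a proper pretest show Δ. Patients with a late pretest show (1 − g)Δ.
- Mean observed change = (1 − f)Δ + f(1 − g)Δ = (1 − f·g)Δ

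The documents give neither f nor g. The values below are assumptions.

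| f | Late pretests out of 140 | g = 25% | g = 50% | g = 100% |
|---|---|---|---|---|
| 10% | 14 | 0.975 | 0.95 | 0.90 |
| 25% | 35 | 0.938 | 0.875 | 0.75 |
| 50% | 70 | 0.875 | 0.75 | 0.50 |

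At f = 40% and g = 100% the factor is 1 − 0.40 = 0.60. The g = 100% column is an upper bound, because it supposes that the interview alone produces the whole effect.

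**4. A yardstick.** The plan gives no sample size calculation for the LMQ. With 140 pairs, two-sided 5% and 80% power, the detectable change is about 2.80/√140 = 0.237 SD of the paired differences. A true change of that size would be estimated at 0.237 × 0.95 = 0.225 SD (f = 10%, g = 50%) or 0.237 × 0.75 = 0.178 SD (f = 50%, g = 50%). The extreme case gives 0.237 × 0.60 = 0.142 SD.

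**5. Direction.** If the interview makes patients more aware of problems with their medicines, late pretests may look worse than true baselines. Then g is negative and the factor exceeds 1, so the improvement is overstated.

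**The case against.** The case on the other side has real weight.

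- **The same-day interview is only one of three options.** Table 1 displays a one-week gap between recruitment and interview. The option is open to all 900 planned patients, most of whom have no pretest. A reader might infer that contaminated pretests are certain. The text does not support that: the number affected is unknown and could be zero. This stands.
- **Contamination is probably partial.** The interview gathers information. Interventions are prepared in step 4 and carried out in step 5, recommended within 2 weeks of the interview. A pretest answered a few days late would usually precede that step. This stands, and it is why g = 100% is a bound and not an estimate.
- **A reader might infer that every outcome is compromised.** Drug-related problems, refill adherence and satisfaction do not use the questionnaire pretest. Falls and emergency visits that have already happened cannot be altered by an interview; at most their recall can. This stands.
- **The subset is exploratory and handling of late forms may be left to a fuller document.** The LMQ is the third outcome, and the checklist and webtool form are not shown. Visit windows are indeed ordinary detail. This part does not answer the point, however: the article states an option that, when followed, breaks its own definition of the pretest, and the order in the field must be settled before analysis.

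**Conclusion.** The conflict is in the current text and needs reconciling. For any questionnaire patient interviewed on the day of consent, a T-1w pretest is impossible and the baseline would ordinarily follow the start of the intervention. The next-visit option does not guarantee a week either. The pre-post comparisons of LMQ, ProMAS and PAM can be biased, and recall of falls and emergency care possibly so.

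The size cannot be fixed from the documents. With g = 50%, the estimated change keeps 0.95 of its true size at f = 10% and 0.75 at f = 50%; the factor of 0.60 at f = 40%, g = 100% is an extreme case. These figures assume that the interview moves answers towards the eventual effect; the bias could also run the other way. The finding does not show that the pre-post results are invalid, nor does it bear on the study's first two outcomes.

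**What to change.** **Change**

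1. Reconcile Recruitment and consent, Intervention, and Tables 3 and 4 so that, for patients who agree to the questionnaires, the interview does not start until the pretest is completed. All other patients keep the same-day option.
2. Record the questionnaire completion date and the interview date, and the order of the two when they fall on the same day.
3. Do not count as baseline any T-1w questionnaire completed after the interview. A same-day questionnaire counts only if it is documented as completed before the interview.
4. For patients already recruited, apply the date rule alone. First confirm that the interview date is available, since the webtool content listed in Table 3 does not name it.
5. Report how many pretests were voided, and add a sensitivity analysis that includes them.

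**Cost**

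The ordering rule and date check are small additions. The real cost is in numbers: Data analysis plans paired tests with listwise deletion, so a patient with a voided pretest drops out of the pre-post comparison. Under the assumed shares of 10%, 25% and 50%, the analysed number would fall to 140 − 14 = 126, 140 − 35 = 105 or 140 − 70 = 70. Recruitment began in December 2016 and was extended only to the end of May, so the ordering rule may come too late for many patients. For them the date check is what remains.

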For one, the target population consists of aged, polymedicated patients. These criteria are in line with the recommended target population for clinical pharmacy services in the Netherlands and UK [23, 24]. This research will provide further insights in the patient population who benefits most of a medication review. For this purpose, also the assistance patients receive in their medicines use, both by professionals, carers and devices such as pill boxes are registered. Secondly attention is drawn to a random patient inclusion in the pharmacy to avoid selection bias. Furthermore, there is an obligatory follow up consultation. In contrast to similar studies, this study not only investigates DRPs and interventions but also focusses on the actual implementation of the interventions [25]. Unlike the study of Holland et al. 2005, this intervention is conducted by trained local community pharmacists with whom the patient has a therapeutic relationship [26]. This real-life context could facilitate the implementation in a later phase. In addition, the feasibility study provided insight in training needs of participants and the feasibility of the study protocol. Another strength of this study is that the outcomes allow insight in both the clinical impact by detecting and resolving drug-related problems as well as the patient perspective on the medication use, medicines experiences and the perceptions on the new service. The systematic review by Loh et al. 2016 has demonstrated there is no evidence that a MR significantly improves overall health related quality of life, possibly due to the generic nature of the instruments used. Therefore, this study is the first to use a medication specific tool, the Living with Medicines Questionnaire, to map the medication related quality of life [19, 27]. In addition, the adherence outcome is both objectively measured as well as using subjective patient questionnaires. A final strength of the study is that it is performed by a consortium of three Belgium universities and the national pharmacy association. This allows a combination of research perspectives.

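### The first post questionnaire is timed from the patient interview, not from step 5 where the interventions are carried out, so a late step 5 weakens the T3w LMQ contrast, and satisfaction is rated before the follow-up

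*Protocol article*

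**What the plan says.** **Where the interventions take place.** The Intervention section of the protocol article places them in the second consultation: "In the fifth step, the pharmacist and patient reconvene to discuss and execute the interventions". The patient also goes through the medication overview at that meeting.

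**When that is.** The date is advisory: "It is recommended to perform this second consultation within 2 weeks after the anamnesis". The follow-up consultation (step 6) is advisory in timing too: "It is recommended to perform this follow up a month after the second patient-pharmacist conversation". The Discussion nevertheless makes the follow-up itself part of the service: "Furthermore, there is an obligatory follow up consultation".

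**When patients are surveyed.** Table 1 puts the interview at T0, step 5 at week 2, a researcher measurement at week 3, step 6 at week 6 and the last researcher measurement at week 12. In Table 4 the LMQ is collected at T-1w, T3w and T12w. The "Patient Satisfaction with Pharmacist Services Questionnaire (PSPSQ) 2.0" is collected at T3w only. ProMAS, PAM, emergency care use and falls are collected at T-1w and T12w only.

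**How the clock is described.** Table 3 gives "3 weeks after the review". The Table 4 caption gives "Data is collected 1 week before the patient interview (T_-1w_), 3 weeks later (T_3_) and 12 weeks after the patient interview (T_12w".

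**The concern.** A posttest should follow the thing it is meant to evaluate. Here the T3w form is tied to the interview, and the step that delivers the interventions has no binding date. Nothing in the article links sending the form to completion of step 5. A patient whose second consultation is late can therefore answer the T3w LMQ before anything found in the review has been acted on with them.

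The Sample size section names the LMQ score as the main outcome of the questionnaire subset, and the article does not say whether T3w or T12w is the leading posttest. A T3w mean that mixes patients before and after step 5 would understate the short-term change.

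Satisfaction raises a separate point that needs no late patients. It is measured once, before the last obligatory contact, so a result reported as satisfaction with the six-step service would claim more than was measured.

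**Working it through.** **1. The timeline on schedule (Table 1, weeks from the interview).**
- Step 5 to T3w: 3 − 2 = 1 week.
- T3w to step 6: 6 − 3 = 3 weeks. As a check, step 5 at week 2 plus a month is 2 + 30.4/7 = 6.3 weeks, which agrees with the week 6 printed in Table 1.
- Step 5 to T12w: 12 − 2 = 10 weeks.

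So the T3w form precedes the interventions only if step 5 is more than 1 week past its recommended limit. The T12w form would precede them only if step 5 slipped beyond week 12. The PSPSQ precedes step 6 for every patient who is on schedule.

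**2. The anchor wording, side by side.**
- Table 1: T0 is the interview, so T3w is week 3 and the margin after an on-time step 5 is 1 week.
- Table 4 caption: the middle time point is given only as three weeks later. Counted from the interview, this is week 3. Counted from T-1w, the point named just before it, it is −1 + 3 = week 2. That equals the recommended limit for step 5 and leaves a margin of 2 − 2 = 0 weeks.
- Table 3: counted from the review, with no step named, although the review runs from T0 to week 6.

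**3. The plan's own figure for the subset.** 35 pharmacies × 12 patients × 2/3 consent × (1 − 0.50) = 140, which reproduces the stated number (also 35 × 4 = 140). The article gives no LMQ effect, SD or power, so the size of any loss can only be illustrated.

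**4. Illustration of the loss at T3w.** Let q be the share answering before step 5, and k the fraction of the full change that the interview alone has already produced in them. Then

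observed mean change = full change × [1 − q(1 − k)].

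Both q and k are assumptions. The worst case is k = 0, where the factor is 1 − q. With k = 0.5 and q = 20% it is 1 − 0.2 × 0.5 = 0.90, the same as q = 10% with k = 0.

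To express this as power, take the paired effect that would give 80% power at n = 140 (two-sided 5%): (1.960 + 0.842)/√140 = 0.237 SD of the change. Power at T3w is then Φ(2.802 × factor − 1.960), ignoring any extra variance from the mixture:

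| q (with k = 0) | Change retained | Power at T3w |
|---|---|---|
| 0% | 100% | 80% |
| 10% | 90% | 71% |
| 20% | 80% | 61% |
| 30% | 70% | 50% |
| 50% | 50% | 29% |

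These rows show how sensitive the contrast is. They do not estimate what happened in this study.

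**The case against.** The best defence is that the order of contacts was designed: on the recommended schedule the T3w form follows step 5, and no text says how often step 5 runs late. That stands, and it makes the bias conditional.

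A reader might go further than the article allows in four ways.

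- **That late patients are untreated at T3w.** They are not. They have had a full interview, the pharmacist may already have done the analysis and spoken with the GP, and interventions are registered throughout the process. The LMQ concerns experience with medicines, which the interview could itself change. What is missing is the discussion and execution of interventions in step 5.
- **That the LMQ evaluation as a whole is compromised.** It is also measured at T12w, about 10 weeks after an on-time step 5, and no text makes T3w the primary contrast. The other pre-post questionnaire outcomes are not collected at T3w at all.
- **That the per protocol analysis keeps late patients in.** The article does not define that set. A definition may sit in a fuller document, so neither inclusion nor exclusion can be asserted.
- **That the clocks of Tables 3 and 4 differ by up to six weeks.** This would require counting from the end of step 6, which puts the form at week 6 + 3 = 9. Table 1 prints it before step 6, so Table 3 is more plausibly shorthand. The ambiguity between week 2 and week 3 in the Table 4 caption is the more natural one.

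One can also defend rating satisfaction soon after step 5: patients on schedule have had both main consultations and the overview, and a 50% questionnaire drop-out is expected. So the PSPSQ reading is valid for what it covers. It does not cover the follow-up.

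**Conclusion.** The point holds as a modest weakness of timing. The first post questionnaire is fixed to the interview, the interventions belong to a step with only a recommended date, and nothing in the article ties one to the other.

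The consequence is limited to the T-1w to T3w change in LMQ, where the bias is towards no effect and grows with the share of late patients. That share is unknown, so no percentage loss can be attributed to the study. The power figures above rest on an assumed share, an assumed effect and no benefit from the interview alone. The T12w LMQ is largely unaffected.

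Two parts need no assumption about late patients. On the printed schedule, the single PSPSQ measurement describes satisfaction up to step 5 and not with the complete six-step service. And the anchor wording in Tables 1, 3 and 4 is not uniform and should be reconciled.

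**What to change.** 1. **Anchor the first post questionnaire to step 5.** Send it one week after the actual second consultation, triggered by the registration that the pharmacist makes at that step (Table 1). The article does not say that the consultation date is stored, so add that field if it is absent. Patients on schedule stay at week 3.
2. **State this anchor identically in Tables 1, 3 and 4.**
3. **For forms already collected,** flag those answered before step 5 and report the T-1w to T3w LMQ change with and without them. This is a weaker fallback, since leaving patients out on the basis of timing can itself select.
4. **Describe the T3w PSPSQ as satisfaction up to step 5.** Optionally repeat it on the existing T12w form and keep the T3w reading alongside.

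**Cost:** small. The first post questionnaire no longer falls at one fixed calendar time from baseline, and the pharmacy must report the step-5 date promptly. A repeated PSPSQ adds a little respondent burden and would miss patients who drop out between T3w and T12w. The timing of the consultations themselves does not change.
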